# Effects of the Active Choices Program on Self-Managed Physical Activity and Social Connectedness in Australian Defence Force Veterans: Protocol for a Cluster-Randomized Trial

**DOI:** 10.2196/21911

**Published:** 2021-02-24

**Keywords:** military service veterans, self-managed physical activity, behavioral support program, psychological well-being, social connectedness, health service utilization, health service costs, physical activity, well-being, health professional, veterans, behavioral, support program

## Abstract

**Background:**

A stepped-down program is one in which clients transition from the care of a health professional to self-managed care. Very little is known about the effectiveness of stepped-down physical activity (PA) programs for military service veterans.

**Objective:**

This study will test Active Choices, a stepped-down behavioral support program designed to help Australian Defence Force veterans and their dependents who are clients of the Department of Veterans’ Affairs, transition from treatment by an exercise physiologist or physiotherapist to self-managed PA.

**Methods:**

The study is a parallel-group, randomized trial, with city-based exercise physiology or physiotherapy practices that recruit eligible Department of Veterans’ Affairs clients assigned to Active Choices or a comparison program. The study aims to recruit 52 participants (26 in each group). The Active Choices program will consist of 2 face-to-face (Weeks 1, 12) and 2 telephone (Weeks 4 and 8) consultations. During these sessions, the participant and Active Choices consultant will utilize an evidence-based resource booklet to review the key benefits of an active lifestyle, build an action plan for PA preferences, set and review goals, self-monitor progress relative to set goals, and discuss strategies to overcome PA barriers. Linking participants to local PA communities to overcome social isolation will be a program priority. The comparison program will consist of 2 consultations (Weeks 1 and 12) and use fewer behavioral support strategies (education, self-monitoring, and action planning only) than Active Choices. Outcome measures will be administered at baseline, end-intervention (12 weeks), and follow-up (24 weeks) to assess changes in moderate intensity self-managed PA, psychological well-being, and social connectedness. We will also measure health service utilization and costs as well as PA choices across the intervention period. End-intervention interviews will capture participant experiences.

**Results:**

Due to the impacts of the COVID-19 pandemic on human research activities in Australia, participant recruitment will commence when it is safe and feasible to do so.

**Conclusions:**

Findings will provide valuable pilot data to support up-scaling of the program and larger effectiveness trials with regional and rural as well as city-based Australian Defence Force veterans and their dependents.

**Trial Registration:**

Australian and New Zealand Clinical Trials Registry (ANZCTR): ACTRN12620000559910; https://www.anzctr.org.au/ACTRN12620000559910.aspx

**International Registered Report Identifier (IRRID):**

PRR1-10.2196/21911

## Introduction

The numerous health and psychosocial benefits that accrue through regular participation in physical activity (PA) are well established [1]. PA is particularly beneficial for older people (≥65 years) and plays an important role in retaining independence and life quality through promoting functional fitness, cognitive function, psychological health and well-being, and social connectivity [2].

While active aging can help maintain holistic health and prevent disease, general practitioners are increasingly referring older patients to PA specialists for the treatment and management of existing health conditions, such as high blood pressure, diabetes, or musculoskeletal issues [3]. In Australia, for example, where referrals to exercise physiologists (EP) and physiotherapists may be government-funded, there has been significant growth in the provision of allied health services to older people. Data from the Department of Veterans’ Affairs (DVA), the Australian Government department that provides support to Australian Defence Force (ADF) veterans and their dependents, many of whom are older adults, indicate that from the period of 2011/2012 to 2016/2017, there was a 51% increase in the number of funded services accessed by DVA clients. This was despite a 19% reduction in the number of DVA clients who were eligible to access allied health services [4]. Service uptake was significantly underpinned by large increases in the number of DVA clients who saw an EP or physiotherapist for treatments involving PA.

The benefits of referral to a PA specialist include receipt of expert care and tailored PA guidance during treatment. However, it has been argued that PA referral programs lack behavior change components that promote longer-term adherence [5]. Consequently, such programs do not enable or create channels for patients to “step-down” to self-managed PA after a course of allied health treatment. A stepped-down program is one in which patients transition from allied health care to self-managed behavior [6]. Thus, individuals take responsibility for initiating and maintaining their own PA regimes, instead of being dependent on supervision from a PA specialist.

Given the significant range of health disparities between military service veterans and the general population, stepped-down programs that promote self-management offer a means to support ongoing engagement in PA [7]. It is also the case that self-management is challenging and greater support for sustainability is obtained through engagement in PA with others [8]. This may have the added benefit of helping veterans deal with challenges of social disconnection that can come from losing long-standing connections to peers and support networks that enable positive health behaviors [9]. Engaging veterans in health promotion programs that emphasize social connectivity through PA may be an effective strategy not only for sustainability of PA but also for re-establishing social support networks that can help counter feelings of isolation and ill-health [10].

Recognizing the need to develop, implement, and evaluate scalable interventions that can empower healthy lifestyle choices and social connectivity for military service veterans, the aim of this study is to test “Active Choices,” a stepped-down behavioral support program for ADF veterans and their dependents. The 12-week program seeks to connect and engage participants with their local active communities as they transition from DVA-supported treatment by an EP or physiotherapist to self-managed PA. This proof-of-concept study will determine the impacts of the Active Choices program on clients’ moderate intensity self-managed PA, psychological well-being, and social connectedness and explore the potential effects on health service utilization and costs. The acceptability and feasibility of the program will also be examined.

## Methods

### Study Design and Setting

The study is a 24-week, parallel-group, randomized trial for DVA clients (ADF veterans and their dependents) who have been cleared by their treating EP or physiotherapist as able to safely transition to self-managed PA. EP or physiotherapist practices that we engage to recruit eligible participants will be randomly assigned to the Active Choices or comparison program, using an allocation ratio of 1:1.

Randomization will be performed using a simple randomization procedure, based on a computer-generated sequence. Allocation of practices will be concealed at the time of assignment, and members of the research team who will analyze the study data will be blinded to allocation. However, blinding of participants and those who will administer the interventions and outcome assessments will not be possible due to the nature of the program.

Data will be collected from participants at 3 timepoints: baseline, end-intervention (Week 12), and follow-up (Week 24). The trial will be conducted in Brisbane, Australia. Intervention delivery and data collection will take place at the allied health practice the participant attends. A flow chart of the trial is shown in Figure 1.

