### Sample Size

The reference parameters used to calculate the sample size were based on a recent large-scale survey conducted by our team, which examined accelerometer-measured PA in nearly 700 adults living in Brisbane, Australia. This study found participants accumulated an average of 10 minutes/day (70 minutes/week) of at least moderate intensity PA [11]. For our study, sample size was calculated based on change in accelerometer-measured PA, from baseline to 24 weeks, between the 2 groups, in order to detect a minimum average increase of 11 minutes/day (77 minutes/week) of moderate intensity PA. In addition to the PA observed in our reference study [11], this is equivalent to the minimum amount required to achieve standard Australian PA recommendations of 150 minutes/week of moderate intensity PA [12]. Assuming an average of 10 minutes/day (standard deviation of 12.7 minutes/day) at baseline, power of 80%, and significance level of 5%, our power analysis determined that a minimum sample size of 42 (21 in each group) is needed to detect a minimum average increase of 11 minutes/day in moderate intensity PA. To allow for 20% loss to follow-up and 10% noncompliance with PA device use, 52 participants will be recruited to the study (26 in each group).

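### Simple randomisation of practices does not protect the planned 1:1 split with 26 per group, and leaves balance of practice type and size to chance

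*Protocol article*

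**What the plan says.** Under Study Design and Setting, the practice is the unit of allocation: "EP or physiotherapist practices that we engage to recruit eligible participants will be randomly assigned to the Active Choices or comparison program". The same sentence sets equal allocation, "using an allocation ratio of 1:1". The next paragraph names the method: "Randomization will be performed using a simple randomization procedure, based on a computer-generated sequence". It mentions no blocking, stratification, matching or minimisation.

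Under Sample Size, the power calculation concludes that "a minimum sample size of 42 (21 in each group) is needed", and after an allowance for losses "52 participants will be recruited to the study (26 in each group". Both figures are per arm and equal.

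Recruitment and Eligibility Criteria shows that two kinds of practice will be approached, exercise physiology and physiotherapy, all in Greater Brisbane. The article gives no number of practices, no expected clients per practice and no recruitment quota by arm. Data Analyses states that the mixed model will account for the clustered design, and names no adjustment for practice type or size.

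**The concern.** A 1:1 ratio under simple randomisation describes the probability for each practice, not the result. With many individually randomised people the two nearly coincide. With a modest number of practices they often do not, and every practice that lands on the heavier side brings all of its clients with it. The article's power rests on equal arms, so the stated method and the stated group sizes fit each other badly. This is a method that the article fixes, not a detail left to a fuller document.

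Two things are at stake. Unequal arms estimate the treatment difference less precisely than equal arms of the same total. Nothing steers the two professions, or large and small practices, evenly across arms, and with few practices a model can correct for little of this afterwards. Profession bears on what is measured: time in supervised treatment is subtracted from the primary outcome (Primary Outcome Measure), and use and cost of exercise physiology and physiotherapy services are themselves assessed (Health Service Data).

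**Working it through.** **Inputs from Sample Size:** difference 11 min/day, "standard deviation of 12.7 minutes/day", power 80%, significance level 5% (two-sided assumed; it reproduces the figure), 42 analysed. **Assumed, because not stated:** number of practices K from 4 to 26; equal yield per practice; no intracluster correlation; no per-arm quota.

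**1. The plan's own figure.** n per arm = 2(1.960 + 0.842)² × 12.7² / 11² = 20.9, so 21 per arm and 42 in all. Power at 21:21 is Φ(11 / (12.7 × √(1/21 + 1/21)) − 1.960) = Φ(0.847) = 0.801. The figure reproduces.

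**2. Chance of an equal split.** The number of practices in one arm is Binomial(K, 0.5). For even K, P(equal) = C(K, K/2) / 2^K; for odd K it is zero. P(all in one arm) = 2 / 2^K.

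**3. Power for a given split.** With 42 analysed and a split of k₁:k₂ practices, n₁ = 42k₁/K and n₂ = 42k₂/K. Power = Φ(11 / (12.7 × √(1/n₁ + 1/n₂)) − 1.960).

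| Split of practices | Analysed | Variance relative to 21:21 | Power |
|---|---|---|---|
| equal | 21 : 21 | 1.00 | 0.80 |
| 5:3 | 26.25 : 15.75 | 1.07 | 0.78 |
| 4:2 | 28 : 14 | 1.13 | 0.75 |
| 6:2 | 31.5 : 10.5 | 1.33 | 0.68 |
| 5:1 | 35 : 7 | 1.80 | 0.55 |

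**4. Power averaged over all allocations.** Weight each split by its binomial probability and count zero when all practices fall in one arm. For K = 4: (6/16)(0.801) + (8/16)(0.681) + (2/16)(0) = 0.641.

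| K | P(equal split) | P(all in one arm) | Average power |
|---|---|---|---|
| 4 | 0.375 | 0.125 | 0.64 |
| 6 | 0.312 | 0.031 | 0.71 |
| 8 | 0.273 | 0.008 | 0.74 |
| 12 | 0.226 | 0.0005 | 0.76 |
| 20 | 0.176 | <0.0001 | 0.78 |
| 26 | 0.155 | <0.0001 | 0.785 |

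**5. Practice type.** Suppose there are 4 practices of each type (assumed). Each type splits 2:2 with probability 6/16, so both do with probability 0.375² = 0.14.

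**6. Does blocking alone repair it?** A simulation let practice sizes vary (coefficient of variation 0.65, assumed) and shared 52 recruits among 8 practices. The chance of 24 to 28 recruits per arm is 0.16 under simple randomisation and 0.28 under an exact 4:4 split. Blocking helps but does not secure 26 per group.

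**The case against.** The strongest reply is that the typical loss is small. With 8 practices, (70 + 112)/256 = 71% of allocations are 4:4 or 5:3, and 5:3 still has power 0.78. By 20 practices the average loss is about 2 points. The number of practices is nowhere given, so that there will be few of them is an inference from 52 participants in one city. This stands, and it is why the averages above matter more than the bad splits.

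The second reply is that 26 per group is a recruitment target. Practices need not contribute equally, and an arm with fewer practices could recruit more clients from each. This also stands: a reader might infer that 26 per group is unattainable, and the article does not support that. But it states no quota by arm, and a quota would not balance profession or practice characteristics. Nor would it restore the number of practices: if practices differ, the treatment difference carries a variance term proportional to 1/k₁ + 1/k₂. For 6:2 that sum is 0.667, against 0.5 for 4:4, however many clients each practice supplies.

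Third, a reader might infer that profession is confounded with treatment and biases the result. That goes too far. Simple randomisation is valid, any imbalance is due to chance, and nothing in the article shows that practice type or size predicts the outcome. In both arms the consultations are given by an Active Choices consultant.

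Finally, the study calls itself proof of concept and expects to yield pilot data, which lowers the weight of a modest power loss. It does not remove the point, because the article also sets 80% power and tests main effects at 5%.

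**Conclusion.** The point holds as a mismatch between a stated method and a stated plan. An equal split of practices has probability of at most 0.375 for any number from 4 to 26, so that conclusion does not depend on guessing the number. The size of the harm does depend on it. Average power is about 0.64 with 4 practices, 0.71 with 6, 0.74 with 8 and 0.76 to 0.78 with 12 to 20. These figures assume equal practice sizes, 42 analysed, no clustering and no quota. Values of 0.68 or 0.55 belong to particular bad splits and should not be read as the expected result. The one catastrophic outcome, all practices in one arm, is a real risk only with very few practices: 0.125 with 4 and 0.03 with 6. The consequence is lost precision and chance imbalance between practices, not systematic bias. Restricted allocation should replace the present method, but the present method does not invalidate the trial.

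**What to change.** In Study Design and Setting, replace simple randomisation with restricted allocation of practices. Randomise them in one or a few concealed batches after they have been engaged, stratified or constrained on practice type (exercise physiology or physiotherapy) and on the expected number of eligible DVA clients. Expected client numbers need to be part of the restriction, because blocking on the count of practices alone does not secure 26 per group when practice sizes vary. In Data Analyses, say that the mixed model will account for the allocation factors as far as the number of practices allows.

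The cost is more than a change of wording. Practices must be engaged, and approximate client numbers obtained, before any is allocated, which has to fit the 3-month recruitment target in Results. If practices are instead allocated one after another in blocks, the sequence becomes slightly more predictable. The timing is favourable: according to Results, participant recruitment had not begun, and imbalance between practices cannot be undone once they are allocated.

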**Figure 1 figure1:**
[figure not shown]
Participant flow through the trial. EP: exercise physiology; PA: physical activity.

### Sample Size

The reference parameters used to calculate the sample size were based on a recent large-scale survey conducted by our team, which examined accelerometer-measured PA in nearly 700 adults living in Brisbane, Australia. This study found participants accumulated an average of 10 minutes/day (70 minutes/week) of at least moderate intensity PA [11]. For our study, sample size was calculated based on change in accelerometer-measured PA, from baseline to 24 weeks, between the 2 groups, in order to detect a minimum average increase of 11 minutes/day (77 minutes/week) of moderate intensity PA. In addition to the PA observed in our reference study [11], this is equivalent to the minimum amount required to achieve standard Australian PA recommendations of 150 minutes/week of moderate intensity PA [12]. Assuming an average of 10 minutes/day (standard deviation of 12.7 minutes/day) at baseline, power of 80%, and significance level of 5%, our power analysis determined that a minimum sample size of 42 (21 in each group) is needed to detect a minimum average increase of 11 minutes/day in moderate intensity PA. To allow for 20% loss to follow-up and 10% noncompliance with PA device use, 52 participants will be recruited to the study (26 in each group).

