### Data Analyses

Baseline descriptive statistics will be used to summarize the demographic, physical, and lifestyle behavior characteristics of participants, and data will be checked for parametric assumptions. Intention-to-treat analyses will be conducted using linear mixed effects models. This approach will be used to account for the repeated outcome measures over time and the clustered design of the study and will provide estimates on the within-group and between-group changes in accelerometer-measured moderate intensity PA, psychological well-being, and social connectedness. Sensitivity analyses will be conducted to assess the robustness of findings, and for exploratory purposes, subgroup analyses will be performed by gender, age group, and treatment history. The results of all comparative analyses will be presented with 95% confidence intervals, and statistical significance for main effects will be assessed at the 5% level. Statistical analyses will be conducted using Stata (v15; StataCorp LLC, College Station, TX).

To analyze cost consequences, we will determine the costs of Active Choices and of normal treatment alone, inclusive of both the direct costs of implementing the intervention and the implied cost to the DVA (such as the higher or lower utilization of EP or physiotherapist services relative to group allocation). Difference-in-difference analysis will be used to determine whether Active Choices contributes to cost savings, due to a possible reduction in service utilization.

Consistent with recognized guidelines for qualitative data analyses [20], members of our research team will thematically analyze and independently review interview data and discuss the range of responses to agree on key themes. We will use this qualitative approach to triangulate our findings from the statistical analyses (eg, the impacts of the program on self-managed PA) and determine the factors that encouraged or discouraged engagement with the Active Choices program.

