## Discussion

The purpose of this study is to test Active Choices, a stepped-down behavioral support program to help DVA clients (ADF veterans and their dependents) self-manage PA as they transition from treatment by an EP or physiotherapist. Findings from the systematic review recently conducted by our research group suggest that such programs have the potential to promote short-term PA changes in US military service veterans with high-risk comorbidities (eg, diabetes, posttraumatic stress disorder, musculoskeletal disorders). Among those selected studies that compared a stepped-down intervention to a “usual care” group (n=14), 79% of studies (11/14) observed a positive between-group intervention effect, with the mean magnitude of change being 53 minutes/week of self-reported moderate intensity PA [14].

While this evidence is promising, our review identified no studies with ADF veterans. Similarities may well exist with US military service veterans; however, there is no direct evidence of generalizability to the Australian context or indeed outside of the United States to military service veterans in other countries. The proposed study will therefore contribute important evidence to an identified research need, and the findings provide valuable pilot data to inform larger effectiveness trials at the national level. Beyond this, our study will also address other limitations in the veteran evidence base. These include the use of self-report rather than objective measures of PA change and importantly, lack of data concerning the extent to which self-managed PA programs can benefit the psychological well-being and social connectedness of veterans or their dependents.

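### The sample size of 42 at 80% power carries no allowance for randomising practices, so the stated power is not supported for this design

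*Protocol article*

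**What the plan says.** The title of the protocol article ends "Protocol for a Cluster-Randomized Trial". Study Design and Setting confirms the unit of allocation: "EP or physiotherapist practices that we engage to recruit eligible participants will be randomly assigned to the Active Choices or comparison program". Practices are allocated to the two arms in equal proportion. Data Analyses states that the linear mixed models are chosen to "account for the repeated outcome measures over time and the clustered design of the study".

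Sample Size bases the calculation on the change in accelerometer-measured activity from baseline to 24 weeks, compared between the two groups, "in order to detect a minimum average increase of 11 minutes/day (77 minutes/week) of moderate intensity PA". Its inputs are 80% power, 5% significance and a reference distribution: "Assuming an average of 10 minutes/day (standard deviation of 12.7 minutes/day) at baseline". The result is that "our power analysis determined that a minimum sample size of 42 (21 in each group) is needed". The target is then raised to 52 (26 per group) for 20% loss to follow-up and 10% noncompliance with the device.

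The section names no ICC, number of practices, participants per practice or design effect.

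**The concern.** Participants from the same practice tend to resemble one another. Here they are selected by the same clinicians and receive the program at the same site, and in the Active Choices arm they may be linked with other participants in their area. When practices are randomised, this resemblance inflates the variance of the between-group difference. With few practices, the test also has few degrees of freedom. A calculation that ignores both effects overstates power.

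The article commits to a design and an analysis that recognise clustering, but its one quantitative justification of size does not. Planning for clustering in the analysis protects the validity of the test; it does not restore the planned power. A non-significant week-24 result could be read as coming from a trial with 80% power. The article also offers its findings as pilot data for larger trials, so the same method could be carried forward.

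**Working it through.** **Inputs from the article.** Difference 11 min/day; SD 12.7 min/day; power 80%; significance 5%, taken as two-sided; stated result 21 per group; recruited 52.

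**Step 1: reproduce the stated figure.** For two individually randomised groups,

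n per group = 2 × (1.960 + 0.842)² × 12.7² / 11² = 20.92, rounded up to 21, or 42 in total.

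This matches exactly with a design effect of 1. The power of 21 per group follows from the standard error 12.7 × √(2/21) = 3.919: 11/3.919 = 2.807, and Φ(2.807 − 1.960) = 80.1%.

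**Step 2: look for an allowance in the 52.** 42/0.8 = 52.5, so the 20% loss alone uses up the increase. Nothing is left for clustering.

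**Step 3: add clustering.** The ICC and number of practices are not in the article, so I assume ICC 0.02 to 0.10 and k = 6, 8 or 12 practices, split equally with equal cluster sizes, and 42 analysed. Then m = 42/k and the design effect is DE = 1 + (m − 1) × ICC. Power is Φ(11 / (12.7 × √(2 × DE/21)) − 1.960). The small-sample version uses a noncentral t distribution with k − 2 degrees of freedom.

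| Practices | ICC | DE | Power, normal | Power, k − 2 df |
|---|---|---|---|---|
| 6 | 0.02 | 1.12 | 76% | 52% |
| 6 | 0.05 | 1.30 | 69% | 47% |
| 6 | 0.10 | 1.60 | 60% | 40% |
| 8 | 0.02 | 1.085 | 77% | 62% |
| 8 | 0.05 | 1.21 | 72% | 57% |
| 8 | 0.10 | 1.425 | 65% | 50% |
| 12 | 0.02 | 1.05 | 78% | 70% |
| 12 | 0.05 | 1.125 | 75% | 67% |
| 12 | 0.10 | 1.25 | 71% | 62% |

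Worked example, 8 practices and ICC 0.05: m = 5.25; DE = 1 + 4.25 × 0.05 = 1.2125; standard error 3.919 × √1.2125 = 4.316; 11/4.316 = 2.549; Φ(0.589) = 72%. With 6 df it is 57%.

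Rounding up to 21 leaves room only for a design effect of 21/20.92 = 1.004. So, on the article's SD, in practice any positive ICC with more than one participant per practice takes power below 80%.

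**Step 4: number needed in the example.** With 8 practices fixed, cluster size grows with n, so n = 20.92 × (1 + (2n/8 − 1) × 0.05). This gives n = 19.87/(1 − 0.2615) = 26.9, or 27 analysed per group (26 gives 79%). With 6 df the requirement is about 47 per group.

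**Step 5: the SD.** The outcome is change, but 12.7 is a baseline SD. If the SD is the same at both times and r is the baseline to week-24 correlation, the SD of change is 12.7 × √(2(1 − r)), which equals 12.7 only at r = 0.5. In the same example:

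| r | SD of change | Power, normal | Power, 6 df |
|---|---|---|---|
| 0.4 | 13.9 | 64% | 50% |
| 0.5 | 12.7 | 72% | 57% |
| 0.6 | 11.4 | 81% | 66% |
| 0.7 | 9.8 | 91% | 78% |

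**The case against.** The strongest reply is that the shortfall is not proven. Its size rests on an ICC and a practice count that the article does not give. At ICC 0.01 with 6 to 12 practices the normal approximation loses only 1 to 2 points. A within-person correlation above 0.5 would shrink the SD of change and could offset some or, as Step 5 shows under the normal approximation, all of the loss. This stands as a limit on the conclusion. It does not rescue the calculation, because the article states no correlation and claims no offset, and a correlation below 0.5 would make matters worse.

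A second reply is that this is a proof-of-concept study whose mixed model handles the clustering and whose comparisons will be reported with 95% confidence intervals. That is correct, and the planned analysis is not invalidated. But the Sample Size section still claims 80% power for a between-group comparison, and that claim is what fails.

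A third reply is that a journal article condenses the full protocol. Condensation cannot explain this case: the inputs and the result are both printed, and they agree only if clustering is left out.

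Two stronger readings are tempting and should not be drawn:

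- **Zero gain in the comparison group.** Because 11 min/day is motivated as the gain needed to reach the guideline level, a reader might infer that the power assumes no improvement in the comparison arm. The section defines the target as a difference in change between the groups, and power for a given difference does not depend on what the comparison group gains.
- **The review's smaller effect.** The Discussion reports "the mean magnitude of change being 53 minutes/week of self-reported moderate intensity PA", which is below 77 minutes/week. That figure is self-reported, from US veterans and against usual care. This trial uses accelerometer data net of supervised activity, against an active comparison program. The two are not comparable, so the review figure does not show the target to be wrong.

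**Conclusion.** The point holds as a statement about support for the claim. The 42 is the unclustered result, the 52 adds nothing for clustering, and the 80% is therefore not justified for a trial that randomises practices.

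If 12.7 is the SD of change, 42 are analysed, and there are 6 to 12 equal-sized practices with ICC 0.02 to 0.10, power is about 78% to 60% by the normal approximation and 70% to 40% with practices-minus-2 degrees of freedom. The second range is the more realistic guide with so few clusters: even at ICC 0 it gives only about 57%, 65% and 72% for 6, 8 and 12 practices.

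A reader might go further and infer that the trial's power is demonstrably below 80%. The article does not support that, because the ICC, the practice count and the SD of change are all unstated.

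**What to change.** Restate the Sample Size paragraph with the planned number of practices, the expected participants per practice, an ICC range, the design effect 1 + (m − 1) × ICC, degrees of freedom suited to few clusters, and an explicit SD of change with the correlation it assumes. Then either report the power, or the detectable between-group difference, that 52 recruited participants give across that range, or withdraw the 80% claim and justify 52 on feasibility and on the expected width of the confidence interval.

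Spreading the same 52 participants over more practices would recover part of the lost power. At ICC 0.05 with 42 analysed, going from 6 to 12 practices raises it from 69% to 75% (normal) or from 47% to 67% (k − 2 df), still short of 80%.

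The cost is one rewritten paragraph and a less favourable stated power. No additional participants are needed if the 80% claim is dropped; keeping it would require more participants, more practices, or a documented smaller SD of change. The article reports that participant recruitment has not begun, so the change can be made in time.

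### The 52 recruits cover about 19% total loss, not the 20% loss to follow-up plus 10% device noncompliance they are said to cover; at those rates about 36 to 37, not 42, would have valid week 24 accelerometry

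*Protocol article*

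**What the plan says.** The Sample Size section bases the calculation on the between-group difference in change in accelerometer-measured activity from baseline to 24 weeks, "in order to detect a minimum average increase of 11 minutes/day (77 minutes/week) of moderate intensity PA". The variability input is given as "Assuming an average of 10 minutes/day (standard deviation of 12.7 minutes/day) at baseline", and the error rates as "power of 80%, and significance level of 5" percent. Study Design and Setting gives the split between arms, "using an allocation ratio of 1:1". The result is "a minimum sample size of 42 (21 in each group) is needed".

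The next sentence inflates that number for two named causes of missing data: "To allow for 20% loss to follow-up and 10% noncompliance with PA device use, 52 participants will be recruited to the study", with 26 per group. The Methods paragraph of the abstract repeats the target, "The study aims to recruit 52 participants (26 in each group"), without mentioning attrition or power.

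Accelerometer Data Processing gives the wear rule: a recording counts only with at least 600 minutes of wear per day on 4 or more days.

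**The concern.** The sentence names two allowances, but the step from 42 to 52 has room for only one. Both causes remove the quantity on which the sample size rests. A participant who drops out before week 24 has no week 24 recording. One who attends but fails the wear rule has a recording that cannot be used. Device noncompliance is therefore a loss on top of dropout, and the plan lists it separately.

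If both happen at the stated rates, the number with a valid week 24 primary measurement falls below the minimum that the plan sets for itself, and the 80% power it claims is not delivered under its own assumptions. The recruitment target fixes the size of the trial, so it should agree with the rates given beside it.

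**Working it through.** **Inputs** (Sample Size and Study Design and Setting): difference 11 minutes/day; SD 12.7 minutes/day; power 80%; significance level 5%; 1:1 allocation; loss to follow-up 20%; device noncompliance 10%; target 52. Sidedness is not stated. Two-sided is assumed, and it reproduces the plan's 42.

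**1. Reproduce the 42.** Normal approximation for two means:

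n per group = 2 × [SD × (z₀.₉₇₅ + z₀.₈₀) / δ]² = 2 × [12.7 × (1.960 + 0.842) / 11]² = 20.92, rounded up to 21, so 42 in total.

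This matches. (A t-test calculation gives 22 per group, 44 in total.) Only the inflation step is in question.

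**2. Inflate 42 by the stated rates.**

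| Method | Result |
|---|---|
| Both losses, sequential: 42 / (0.80 × 0.90) | 58.3; 29.2 per group, so 30 per group = 60 |
| Both losses, additive: 42 / 0.70 | 60 |
| Both, multiplied up instead of divided: 42 × 1.3 | 54.6 |
| Both, multiplied up in turn: 42 × 1.2 × 1.1 | 55.4 |
| 20% only, divided: 42 / 0.80 | 52.5 |
| 20% only, multiplied up per group: 21 × 1.2 = 25.2, rounded up to 26 | 52 |

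No method that applies both rates as separate losses reaches 52, not even the usual shortcut of multiplying up. The 20% allowance alone does.

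**3. Work back from 52.** Total loss accommodated: 1 − 42/52 = 19.2%.

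**4. Expected number with valid week 24 data.**
- Additive: 52 × 0.70 = 36.4 (18.2 per group).
- Sequential: 52 × 0.80 × 0.90 = 37.4 (18.72 per group).

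**5. Power at those numbers**, with the plan's own difference and SD, two-sided 5%. Normal approximation: power = Φ(δ / (SD × √(2/n)) − 1.960). The t-test column uses the noncentral t with 2n − 2 degrees of freedom.

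| n per group | Normal approximation | t-test |
|---|---|---|
| 21 (as planned) | 80.1% | 78.2% |
| 18.72 (sequential) | 75.5% | 73.2% |
| 18.2 (additive) | 74.3% | 71.9% |

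Compared within a column, the loss is 4.6 to 5.8 points (normal) or 5.0 to 6.3 points (t-test), so about 5 to 6 points either way.

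**6. Check the number that would suffice.** 60 × 0.70 = 42 and 60 × 0.72 = 43.2, so 60 holds under both readings. 58 does not: 58 × 0.72 = 41.8 and 58 × 0.70 = 40.6.

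**The case against.** **The 10% may lie inside the 20%.** If every participant who does not comply with the device is also counted among those lost, 52 × 0.80 = 41.6, about 42. So it would be too strong to infer that no reading yields 52. But the text does not state this reading, it joins the two rates as separate items, and the reading would make the 10% redundant. If it was meant, the sentence still needs rewording.

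**Participants without week 24 data are not discarded.** Data Analyses specifies intention-to-treat linear mixed models over the repeated measurements, so someone with valid baseline and week 12 recordings still contributes. This stands. A reader might infer that only 36 to 37 people will be analysed; the documents do not support that. The figure is the number expected to have valid week 24 accelerometry, which is the basis of the sample size. How much the partial data recover depends on within-person correlation, which is not given.

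**The study is a pilot.** The article calls it proof-of-concept, and Data Analyses reports comparisons with 95% confidence intervals. This limits the severity: a shortfall of this size does not bias the estimate or undermine the design. It does not remove the error, because the plan claims 80% power and tests at the 5% level.

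**The article is condensed.** That does not apply here. Both rates, the starting number and the target are all stated, and they disagree.

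**Conclusion.** The concern holds in this form: 52 recruits do not allow for both stated losses while retaining 42. They allow for about 19% in total. With the two rates as separate losses, about 36 to 37 participants would have valid week 24 accelerometer data, and planned power is about 74-75% instead of 80.1% (normal approximation), or about 72-73% instead of 78.2% (t-test).

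This rests on a two-sided test, on the plan's difference and SD taken as given, and on the two losses not being nested. It concerns the planning calculation only.

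Two stronger inferences are not supported. Setting the t-test figure of 72-73% against the nominal 80% would overstate the loss by about 2 points, because the t-test power at 21 per group is already 78.2%. Quoting a still lower power after clustering by practice would need an intracluster correlation and a number of practices, neither of which the article gives; clustering is a separate question and does not follow from this arithmetic.

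The sentence should be corrected, but the shortfall is moderate.

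**What to change.** Correct the inflation sentence in Sample Size in one of two ways.

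1. If the losses are separate: keep 52, state that about 36 to 37 participants with valid week 24 data are expected, and give the corresponding power, about 74-75% by the normal approximation and before clustering. Add that 60 recruits (30 per group) would be needed to retain 42 at the stated rates.
2. If the 10% was meant to fall within the 20%, say so, so that the single 20% allowance and the 52 agree.

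The abstract needs changing only if the recruitment target itself changes, since it gives 52 without any attrition or power claim.

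Keeping 52 costs a change of wording and a slightly less favourable stated power. Moving to 60 would mean 8 more participants. The Results section says participant recruitment had not yet begun, so at the time of the article either course was open.
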